# Radiation therapy before radical cystectomy combined with immunotherapy in locally advanced bladder cancer – study protocol of a prospective, single arm, multicenter phase II trial (RACE IT)

**DOI:** 10.1186/s12885-019-6503-6

**Published:** 2020-01-03

**Keywords:** Bladder cancer, Urothelial cancer, Transitional cell carcinoma, Locally advanced, Immunotherapy, Radiotherapy, Radical cystectomy, Nivolumab, Checkpoint inhibitor, PD-1 inhibitor

## Abstract

**Background:**

Patients with locally advanced bladder cancer (cT3/4 cN0/N+ cM0) have a poor prognosis despite radical surgical therapy and perioperative chemotherapy. Preliminary data suggest that the combination of radiation and immunotherapy does not lead to excess toxicity and may have synergistic (abscopal) anti-tumor effects. We hypothesize that the combined preoperative application of the PD-1 checkpoint-inhibitor Nivolumab with concomitant radiation therapy of the bladder and pelvic region followed by radical cystectomy with standardized lymphadenectomy is safe and feasible and might improve outcome for patients with locally advanced bladder cancer.

**Methods:**

**Study design: “**RACE IT” (AUO AB 65/18) is an investigator initiated, prospective, multicenter, open, single arm phase II trial sponsored by Technical University Munich. Study drug and funding are provided by the company Bristol-Myers Squibb.

**Study treatment:** Patients will receive Nivolumab 240 mg i.v. every 2 weeks for 4 cycles preoperatively with concomitant radiation therapy of bladder and pelvic region (max. 50.4 Gy). Radical cystectomy with standardized bilateral pelvic lymphadenectomy will be performed between week 11–15.

**Primary endpoint:** Rate of patients with completed treatment consisting of radio-immunotherapy and radical cystectomy at the end of week 15.

**Secondary endpoints:** Acute and late toxicity, therapy response and survival (1 year follow up).

**Main inclusion criteria:** Patients with histologically confirmed, locally advanced bladder cancer (cT3/4, cN0/N+), who are ineligible for neoadjuvant, cisplatin-based chemotherapy or who refuse neoadjuvant chemotherapy.

**Main exclusion criteria:** Patients with metastatic disease (lymph node metastasis outside pelvis or distant metastasis) or previous chemo-, immune- or radiation therapy.

**Planned sample size:** 33 patients, interim analysis after 11 patients.

**Discussion:**

This trial aims to evaluate the safety and feasibility of the combined approach of preoperative PD-1 checkpoint-inhibitor therapy with concomitant radiation of bladder and pelvic region followed by radical cystectomy. The secondary objectives of therapy response and survival are thought to provide preliminary data for further clinical evaluation after successful completion of this trial. Recruitment has started in February 2019.

**Trial registration:**

Protocol Code RACE IT: AB 65/18; EudraCT: 2018–001823-38; Clinicaltrials.gov: NCT03529890; Date of registration: 27 June 2018.

## Background

Bladder cancer is the 9th most common cancer worldwide with about 430,000 new cases each year. About 25% of patients present with muscle-invasive disease at the time of diagnosis [1]. The current standard of care for muscle-invasive bladder cancer (MIBC) is radical cystectomy with pelvic lymphadenectomy. According to German and European guidelines, neoadjuvant chemotherapy is recommended for patients with MIBC, who are fit to receive cisplatin-based chemotherapy [2, 3]. Unfortunately, around 50% of patients are ineligible to receive neoadjuvant chemotherapy mainly because of impaired renal function [4].

Patients with locally advanced bladder cancer (cT3/4 cN0/N+ cM0) have a poor prognosis despite radical surgical therapy and systemic treatment. If tumor invades perivesical tissue (pT3), 5-year overall survival (OS) is about 43% and drops as low as 28% in case of infiltration of surrounding tissue (pT4). If tumor has spread to local lymph nodes, only every 5th patient will survive 5 years after surgery [5]. The addition of perioperative chemotherapy only adds a small but significant absolute survival benefit to surgery alone in patients with MIBC [6, 7].

Immune checkpoint-inhibitors have shown impressive results in clinical trials in advanced bladder cancer, leading to FDA and EMA approval as first and second line therapy in metastatic urothelial cancer. Targeting the immune checkpoints “programmed death ligand-1” (PD-L1), “programmed cell death protein-1” (PD-1) and “cytotoxic T-lymphocyte associated protein 4” (CTLA-4) with antibodies leads to T-cell activation and anti-tumor immune response [8]. In Europe the PD-1/PD-L1 inhibitors Nivolumab, Pembrolizumab and Atezolizumab are approved for metastatic bladder cancer [9, 10]. The PD-1 inhibitor Nivolumab was analyzed in the single arm, phase II CheckMate 275 trial, which included 270 evaluable patients with progressive metastatic urothelial cancer after cisplatin-based chemotherapy. Confirmed objective response was achieved in about 20% of patients. Grade 3–4 treatment-related adverse events occurred in 48 (18%) of 270 patients-most commonly grade 3 fatigue and diarrhea. Five deaths were attributed to treatment (pneumonitis, acute respiratory failure, multifactorial acute respiratory failure, septic shock, and cardiovascular failure) [11]. Two current trials are evaluating immune-checkpoint blockade in a neoadjuvant setting (NCT02736266 and NCT02662309) with promising early results [12, 13].

In regard to radiation therapy, neoadjuvant radio (chemo) therapy (RCHT) has shown its efficacy in other tumor entities such as esophageal or colorectal carcinoma [14–16]. In bladder cancer, the sequence of preoperative radio (chemo) therapy (RCHT) followed by radical cystectomy is a common therapy pathway in the setting of trimodal therapy (TMT), which is an accepted alternative treatment for MIBC according to the German S3-guideline [3]. There is promising retrospective data for neoadjuvant RCHT in locally advanced bladder cancer [17]. Since recent preclinical and early clinical trials propose a synergistic effect of radiation and immunotherapy, this combination seems to be an interesting alternative to RCHT [18, 19]. Radiotherapy can lead to immunogenic cell death, which leads to the release and presentation of tumor antigens, which in turn can lead to priming and activation of T-cells. Furthermore, radiotherapy induces antigen presentation and cytokine release of the tumor, which further leads to T-cell recruitment. On the other hand, radiation can induce increased PD-L1 expression in the tumor, hindering the efficiency of attracted T-cells [20]. Currently various clinical phase II and phase III trials explore the combination of radiation therapy and PD-1 inhibition in different tumor entities [18]. Concomitant treatment with PD-L1/PD-1 inhibitors led not only to partial or complete remissions, but also to abscopal (outside the radiation field) effects [20]. Therefore, combined application of radiotherapy with Nivolumab before radical cystectomy might lead to improved cure rates and local control in this otherwise poor prognostic subgroup with locally advanced bladder cancer. Notably, this treatment can be given irrespective of kidney function, which is impaired in 30–50% of these patients [21].

### Aims

The primary objective of RACE IT is to evaluate safety and feasibility of the combined application of preoperative radiation therapy with the PD-1 checkpoint-inhibitor Nivolumab followed by radical cystectomy in patients with locally advanced bladder cancer. We secondarily hypothesize that the combined application of preoperative radiation therapy with the PD-1 checkpoint-inhibitor Nivolumab before radical cystectomy leads to improved disease-free survival (DFS) and overall survival (OS) compared to historical controls.

## Methods and study-design

### Study design

RACE IT is a prospective, multicenter, open, single arm phase II study.

### Inclusion and exclusion criteria

Patients with histologically confirmed, locally advanced bladder cancer (cT3/4, cN0/N+), who are ineligible for neoadjuvant, cisplatin-based chemotherapy or who refuse neoadjuvant chemotherapy can be included in this study. Main exclusion criteria are metastatic disease (lymph node metastasis outside pelvis or distant metastasis) or previous chemo-, immune- or radiation therapy. All inclusion and exclusion criteria are shown in Table 1.

**Table 1 Tab1:** Inclusion and exclusion criteria

Criteria	Details
Inclusion	- Histologically confirmed, locally advanced bladder cancer (cT3/4 cN0/N+ cM0) with ≥10% urothelial differentiation - Ineligibility for neoadjuvant cisplatin-based chemotherapy due to any of the following criteria: • Creatinine Clearance (using the Cockcroft-Gault formula) < 60 mL/min • Hearing loss ≥ grade 2 (CTCAE version 4) • Peripheral neuropathy ≥ grade 2 (CTCAE version 4) • ECOG performance score 2 - Subjects that are eligible for cisplatin may be candidates if they refuse available neoadjuvant cisplatin-based chemotherapy, despite being informed by the investigator about the treatment options. The subject’s refusal must be thoroughly documented. - ECOG 0–2 - Life expectancy > 6 months - Adequate function of bone marrow, liver and coagulation as determined by blood tests - Able to give informed consent - Body weight 35 kg - 160 kg
Exclusion	- Metastatic disease defined as distant metastasis or suspicious lymph nodes outside the pelvis (above aortic bifurcation) using RECIST 1.1 criteria - Prior chemotherapy before treatment (not including intravesical chemotherapy) - Prior radiation therapy of the pelvis - Active, known or suspected autoimmune disease (not including: vitiligo, allergic rhinitis/asthma, type 1 diabetes mellitus, residual hypothyroidism due to an autoimmune condition only requiring hormone replacement, psoriasis not requiring systemic treatment, or conditions not expected to recur in the absence of an external trigger) - Immunosuppressive treatment with corticosteroids or other drugs within 14 days of study drug administration (not including: inhaled or topical steroids and adrenal replacement doses are permitted in the absence of active autoimmune disease) - Experimental therapy or clinical trial at time of inclusion or the previous 4 weeks before inclusion - Previous treatment with an anti-PD-1, anti-PD-L1, anti-PD-L2, anti-CTLA-4 antibody, or any other antibody or drug specifically targeting T-cell costimulation or immune checkpoint pathways (not including BCG therapy) - Any uncontrolled or severe cardiovascular or pulmonary disease determined by the investigator, including i) NYHA functional classification III or IV, congestive heart failure, unstable or poorly controlled angina, uncontrolled hypertension, serious arrhythmia or myocardial infarction in the past 12 months before inclusion; ii) Subjects with interstitial lung disease that is symptomatic or may interfere with the detection or management of suspected drug-related pulmonary toxicity. - End-stage kidney disease defined as GFR < 15 mL/min or need for dialysis - Thromboembolic events like pulmonary embolism or stroke in previous 3 months before inclusion - Other active tumor disease (not including basal cell carcinoma of the skin and carcinoma in situ of the cervix). Tumor is regarded non-active after curative therapy and 5 years of follow up without pathological findings. - Medium to extended surgery or trauma in the previous 4 weeks before inclusion (not including transurethral bladder resection, nephrostomy or ureteral stent or biopsy) - Uncontrolled and serious somatic or mental illness - Pregnant or lactating women - Age < 18 years - Prior organ transplantation - Positive test result for hepatitis B or C indicating acute or chronic infection - Positive HIV test or acquired immunodeficiency syndrome (AIDS) - Gastrointestinal disorders, particularly those with high risk of perforation or fistula formation including i) active peptic ulcer disease or active inflammatory bowel disease (incl. Ulcerative colitis and Crohn’s disease), diverticulitis, cholecystitis, symptomatic cholangitis or appendicitis) during screening and/or ii) history of abdominal fistula or bowel perforation within 6 months prior to first dose of study treatment.

### Endpoints

#### Primary endpoints

Rate of patients with completed treatment consisting of radio-immunotherapy and radical cystectomy at the end of week 15. Completed treatment is defined by administration of at least two complete cycles of Nivolumab with 240 mg i.v. and administration of at least 23 of planned 28 radiation fractions (≥ 41.4 Gy).

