### Treatment and follow up

Treatment starts after successful completion of the screening phase and confirmation of eligibility. Nivolumab 240 mg flat dose will be given intravenously on day 1. Nivolumab will be given every 2 weeks for a total of 4 cycles. The last infusion will be in week 7. Standard radiation therapy will start on day 8 (week 2). The radiation therapy will be given in 28 fractions over approximately 5 and a half weeks. The total dose is 50.4 Gy in fractions of 1.8 Gy per day with 45 Gy of the pelvic region and a consecutive boost of bladder/tumor with 5.4 Gy. Imaging will be performed before start of treatment as baseline and repeated after finishing of study treatment before radical cystectomy to rule out progression or systemic disease. In case of systemic disease, no cystectomy will be performed in curative intention. The surgery consisting of open radical cystectomy with urinary diversion (ileum conduit or neobladder) and standardized pelvic lymphadenectomy will be performed within week 11–15. The standardized lymphadenectomy is exactly defined in a SOP and includes the external and internal iliac region, obturator fossa as well as commune iliac region.

Follow up for secondary endpoints will be starting at the date of cystectomy for 1 year (52 weeks). A schematic outline of the treatment plan is shown in Fig. 1.

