### Statistical calculations for trial sample size

The estimations in regard to the primary endpoint are derived from data from neoadjuvant cisplatin-based chemotherapy followed by radical cystectomy as current standard of treatment. In this regimen, the rate of patients with completed treatment (neoadjuvant therapy and radical cystectomy) is between 90 and 95% [21]. Trials of neoadjuvant radiotherapy in urinary bladder cancer showed no additional postoperative toxicity [2, 3]. Comparing the toxicity of Nivolumab to cisplatin, we assume that a completion rate of 90–95% is a reasonable estimation for the neoadjuvant radio-immunotherapy.

Assuming a rate ≥ 92.5% of patients with completed treatment at the end of week 15, we would tolerate an additional 22.5% of treatment delay (≥ 70% patients with completed treatment at the end of week 15). Thirty patients will be required to reject the null-hypothesis of a rate < 70% patients with completed treatment at the end of week 15 with 82% power and a 2-sided significance level of 5%. Additional 3 patients will be enrolled to account for possible drop-outs. This leads to a panned sample size of 33 patients. Recruitment will be conducted during a period of 2 years.

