### Data analysis

All continuous endpoints will be summarized using descriptive statistics. All categorical endpoints will be summarized using absolute frequencies and percentages.

For the primary endpoint, an exact test for single proportions will be performed to reject the null hypothesis of ≥22.5% of treatment-related delay in surgery at week 15. Proportions will be displayed together with their 90% confidence intervals. If the resulting *p*-value is less than 5%, the study is considered successful. The primary analysis is based on the Full Analysis Set (FAS). Kaplan-Meier curves will be used to describe event-free rates over time (DFS, CSS and OS). Median event-free times will be reported with 95% CI, if the number of events allows the estimation of the median.

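### The primary test is worded for a different event and a different null value from the endpoint that the trial defines and sizes

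*Protocol article*

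**What the plan says.** All references are to the protocol article.

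- **Primary endpoints** (and the Abstract, in the same terms): "Rate of patients with completed treatment consisting of radio-immunotherapy and radical cystectomy at the end of week 15". The next sentence reads "Completed treatment is defined by administration of at least two complete cycles of Nivolumab with 240 mg i.v", and adds a minimum of 23 of the 28 planned fractions. It does not mention cystectomy or week 15 again.
- **Statistical calculations for trial sample size**: the alternative is "Assuming a rate ≥ 92.5% of patients with completed treatment at the end of week 15". The section tolerates a further 22.5% of delay, which it equates with at least 70% completing. Thirty patients are needed to "reject the null-hypothesis of a rate < 70% patients with completed treatment at the end of week 15", with 82% power at a two-sided 5% level. Three more are added for drop-outs.
- **Data analysis**: an exact test of a single proportion on the Full Analysis Set (FAS) is to "reject the null hypothesis of ≥22.5% of treatment-related delay in surgery at week 15". The trial succeeds if p is below 5%.
- **Treatment and follow up**: imaging is repeated before surgery. "In case of systemic disease, no cystectomy will be performed in curative intention".

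**The concern.** The endpoint and the sample size concern completion of a whole sequence. The tested hypothesis concerns "treatment-related delay in surgery at week 15". The two differ in four respects:

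- Delay in surgery says nothing about whether the minimum nivolumab and radiation were delivered.
- The qualifier about relatedness removes late operations judged to have other causes. In an open, single-arm trial that judgement would be made with treatment known.
- Delay is not omission. A patient who never has cystectomy has no obvious place in the tested event.
- The null value is not the one used for the sample size.

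This is the trial's only success criterion. If the same data can be read as positive under one section and negative under another, the conclusion depends on which sentence the analyst follows.

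**Working it through.** **1. The same patient under each wording.**

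| Patient | Endpoint, both sentences read together | Definition sentence alone | Data analysis event |
|---|---|---|---|
| Minimums met, systemic disease found, no cystectomy | Failure | Success | Unclear: surgery omitted, not delayed |
| One nivolumab cycle, cystectomy in week 14 | Failure | Failure | No delay, so not a failure |
| Minimums met, cystectomy after week 15 for an unrelated reason | Failure | Success | Not treatment-related, so not a failure |

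**2. Reproduce the plan's power.** Inputs from the sample size section: n = 30, p0 = 0.70, p1 = 0.925, two-sided 5% (2.5% per tail). With X binomial, P(X ≥ r) = Σ C(n,x) pˣ(1−p)ⁿ⁻ˣ over x = r to n.

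- P(X ≥ 26 | 30, 0.70) = 0.0302, above 0.025.
- P(X ≥ 27 | 30, 0.70) = 0.0093, so the cutoff is 27.
- Power: P(X ≥ 27 | 30, 0.925) = 0.8155, or 81.6% against the stated 82%.

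The alternatives tried do not match: one-sided 5% gives cutoff 26 and power 93.0%, and the two-sided normal approximation gives 89.8%. The stated power therefore belongs to the completion endpoint with a 70% null.

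**3. Where 22.5% comes from.** 0.925 − 0.70 = 0.225, the distance between alternative and null. The failure rate at the null is 1 − 0.70 = 0.30. Used as a null failure rate, 22.5% implies a null success rate of 1 − 0.225 = 0.775.

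**4. Effect of the literal 77.5% null** (2.5% per tail, power at 92.5%).

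| n | Cutoff, 70% null | Power | Cutoff, 77.5% null | Power |
|---|---|---|---|---|
| 30 | 27 | 81.6% | 28 | 60.7% |
| 33 | 29 | 90.2% | 31 | 54.5% |

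For 27/30, doubling the upper tail gives p = 2 × 0.0093 = 0.019 against 70%. Against 77.5% the upper tail is 0.0696, so p = 0.139. The split at 27/30 does not depend on how the two-sided exact p-value is formed: the minimum-likelihood method gives 0.0157 and 0.1256.

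**5. Effect of classifying patients differently, holding the null at 70%.** The Discussion cites two neoadjuvant trials: 7 of 69 without cystectomy (10.1%) and 0 of 55. Carried over as an assumption, this is 0 to about 3 patients (0.101 × 30 = 3.0; 0.101 × 33 = 3.3).

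Moving three patients from success to failure changes the conclusion only if the starting count lies between the cutoff and the cutoff plus 2:

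- n = 30, counts 27 to 29: probability at a true 92.5% is 0.2087 + 0.2758 + 0.2346 = 0.72.
- n = 33, counts 29 to 31: 0.1350 + 0.2220 + 0.2649 = 0.62.

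For example, 31/33 (p = 0.0017) becomes 28/33 (p = 0.083). At 30/30, or at 32 or 33 of 33, the result stands; below the cutoff it was already negative. These ranges use 2.5% per tail. The minimum-likelihood method gives p = 0.0471 at 26/30, which moves the n = 30 range down by one.

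**The case against.** **Loose wording, not a second endpoint.** The Data analysis sentence opens by naming the primary endpoint, and the sample size section already uses delay as shorthand for non-completion. The qualifier may even mean the excess over the expected 7.5% shortfall, since 7.5% + 22.5% = 30%. That is a plausible account of the intent, and no procedure for judging relatedness is described, so the filter is inferred from one adjective. But a single-arm test of one proportion cannot observe an excess. As written, the sentence names both the wrong event and the wrong figure.

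**Three rival endpoints.** A reader might infer that the definition sentence is a further, separate endpoint. The document does not support this. The sentence directly follows one that requires cystectomy by week 15, and it naturally sets minimums for the part of treatment that can be partly delivered. The sample size section also describes completed treatment in the reference regimen as neoadjuvant therapy plus cystectomy. This is an ambiguity; the contradiction is with Data analysis.

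**Three patients reverse the trial.** A reader might infer this from 26/33 against 29/33, with one-sided p-values of 0.182 and 0.0149 against 70%. But those p-values do not use the null that Data analysis implies: against 77.5%, 29/33 gives a one-sided p of 0.107 and also fails. Moreover 29/33 sits exactly at the cutoff, and only one of the two cited trials suggests three affected patients. Reversal is possible but conditional.

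**Detail left to the full protocol.** FAS membership and drop-out handling are commonly left there, and their absence is no fault. The article does, however, state both the endpoint and the tested hypothesis, and the two disagree.

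**Conclusion.** The point holds as one clear contradiction and one ambiguity. The contradiction is that Data analysis tests a different event, at a different null, from the endpoint that is defined and powered. Taken literally, its null raises the cutoff from 27 to 28 of 30 and lowers power from 81.6% to 60.7%; a result of 27/30 would be positive under the sample size section and negative under Data analysis. This rests on exact binomial tests at 2.5% per tail, which is the version that reproduces the stated power, and on reading 22.5% delay as 77.5% success.

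The ambiguity is that the definition sentence does not repeat cystectomy or week 15. The effect of the different event on the count cannot be fixed from the document. An assumed 0 to 3 patients is the range that the two cited trials suggest, and three would change the conclusion only from 27–29 of 30 or 29–31 of 33. Because this is the sole success criterion and the correction is only wording, it should be made before analysis.

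**What to change.** - State one binary variable in Primary endpoints: success means that both stated radio-immunotherapy minimums were met and radical cystectomy was performed by the end of week 15. Every other FAS patient is a failure, whatever the reason.
- In Data analysis, replace the null with a completion rate of at most 70%, and delete the reference to delay in surgery from the hypothesis.
- Report reasons for failure descriptively, including systemic disease without cystectomy and treatment-related delay.

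This needs a few sentences, no new data and no change to treatment. The cost is that the observed rate may be less favourable. The three patients added for drop-outs must also be reconciled with the rule. If all 33 are in the FAS and each completes with probability 92.5%, power is 90.2%. If three drop-outs stay in the FAS as failures and the other 30 complete at 92.5%, reaching 29/33 needs 29 of those 30, with probability 30 × 0.925²⁹ × 0.075 + 0.925³⁰ = 0.2346 + 0.0964 = 0.331. The sponsor should therefore say whether the 92.5% already allows for drop-outs.
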